### Randomization procedures

Patients who provide informed written consent and meet the participant selection criteria will be enrolled and randomized using a 2:1 treatment allocation to either the MBI or control condition. Because the MBI condition is group-based, randomization of participants will be divided into 4 cohorts of 15 participants to reduce the amount of idle time between informed consent and intervention delivery. After the first cohort of 15 participants provides informed consent, they will be randomly assigned either to receive the MBI (*n* = 10) or to a control condition (*n* = 5). The random number function in Excel 2007 software (Microsoft, Redmond, WA, USA) will be used to randomize patients to either the MBI (*n* = 40) or control (*n* = 20) condition using a permuted block randomization scheme to achieve a 2:1 allocation. Within each block size of 15, 10 patients will be randomized to receive the MBI and 5 will be randomly assigned to the wait-listed control condition.

Within 2 weeks of randomization, participants will begin the MBI or their time in the control condition. Following randomization and initiation of the first cohort of 15 patients, the next cohort of 15 patients will be recruited and randomized following the same protocol. This will continue until 60 participants are randomized in a total of 4 cohorts.

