#### Setting and sample

Patients will be recruited from an outpatient comprehensive SCD center in the southeastern United States. An interdisciplinary team of physicians, nurses, psychologists, and social workers run the center, providing care for approximately 600 adults with SCD. The target sample for this pilot study is 60 patients with SCD and chronic pain, with 40 patients randomly assigned to receive the MBI and 20 patients to the control condition. With a sample size of 60, the study does not have 80% power to detect a significant difference between the MBI and control conditions on the primary outcome of pain catastrophizing with a level of significance set a 0.05 (two-tailed). However, the focus of this pilot study is to estimate treatment effect sizes rather than to conduct statistical significance testing.

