### Efficacy

To address aim 2, five valid and reliable patient-reported questionnaires will be administered to determine the effects of MBI relative to the control condition on pain catastrophizing, as well as on pain interference and severity, depression, health-related quality of life (mental and physical health), and mindfulness (Table 3). Each questionnaire will be administered at four time points: week 0 (baseline, prior to initiation of treatment) and weeks 1, 3, and 6. Assessments at weeks 1, 3, and 6 correspond to MBI session 1, session 3, and session 6, respectively.

**Table 3 Tab3:** Instruments and schedule of assessments

Instrument	Abbreviation	Domain	Scale/subscale reliability (Cronbach’s α)	Interpretation^a^	Baseline	Week 1	Week 3	Week 6
Demographic Questionnaire	DEMO	Sociodemographic and clinical characteristics	N/A	N/A	X			
Pain Catastrophizing Scale	PCS	Pain catastrophizing^b^	Total score 0.75 Rumination 0.87 Magnification 0.60 Helplessness 0.79	Low	X	X	X	X
Brief Pain Inventory	BPI	Pain interference and severity	Interference 0.89–0.92 Severity 0.80–0.87	Low	X	X	X	X
Patient Health Questionnaire–9 items	PHQ-9	Depression	Total score 0.87	Low	X	X	X	X
Patient-Reported Outcome Measurement Information System	PROMIS	Physical and psychological health	Mental and physical 0.73–0.96	High	X	X	X	X
Mindful Awareness Attention Scale	MAAS	Mindfulness	Total score 0.87	High	X	X	X	X

*N/A* Not applicable

This table provides the list of questionnaires that will be administered to study participants. Additionally, this table provides details related to when each questionnaire will be administered; the questionnaire’s abbreviation, domain, and psychometrics; and how the questionnaire should be interpreted

^a^Scores representing “improved” functional health status

^b^Primary outcome

Participants will have the option of completing each questionnaire on paper or via an online form. Participants who opt for paper forms will be provided with a packet of questionnaire copies with return envelopes and stamps. Participants who opt for online forms will provide an email address and be emailed hyperlinks that contain exact copies of the paper forms managed by a REDCap database [22]. The order and structure of each measurement will be identical in the paper and online versions. Each assessment packet includes the five questionnaires described in the subsections below. *See* Table 3 for a summary of instruments and schedule of assessments.

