#### Pain Catastrophizing Scale

The Pain Catastrophizing Scale (PCS) will be used to assess pain catastrophizing. The PCS contains 13 items rated on a 5-point scale from 0 (not at all) to 4 (all the time). The total score for the PCS ranges between 0 and 52, with a higher score demonstrating more severe catastrophizing. In addition, the PCS contains three subscales: helplessness (six items), rumination (four items), and magnification (three items) [39]. The PCS was selected as the primary variable of interest in addressing intervention efficacy because it has been studied extensively across many different chronic pain populations and is commonly used as a key outcome in determining the success of interventions that target chronic pain [40, 41]. A total PCS score of 30 represents a clinically relevant level of catastrophizing and corresponds to the 75th percentile of the distribution of PCS scores in clinical samples of chronic pain patients [42]. The PCS total score was the primary outcome.

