### Efficacy

Descriptive statistics will be used to summarize the five measures at baseline and weeks 1, 3, and 6 for randomized participants with at least one outcome assessment completed (observable cases). Tables for unadjusted mean scores for each condition by time will be presented. Random coefficients regression models, a type of hierarchical mixed-effects model for longitudinal data, will be used to evaluate the trajectory of change in pain catastrophizing total scores and other pain-related outcomes. Nonlinear temporal patterns will be fitted as needed. The models will be used to examine the pattern of change in each outcome over time and estimate effect sizes.

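### The 10:5 draw per cohort is valid but leaves balance on baseline PCS to chance; with no stated baseline adjustment, this adds a modest, avoidable error to the effect estimate

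*Protocol article*

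**What the plan says.** All references are to the protocol article.

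- **Sample.** Setting and sample plans 60 patients, "with 40 patients randomly assigned to receive the MBI and 20 patients to the control condition".
- **Draw.** Under Randomization procedures, allocation waits for a full cohort: "After the first cohort of 15 participants provides informed consent, they will be randomly assigned either to receive the MBI". Later cohorts are handled alike: "the next cohort of 15 patients will be recruited and randomized following the same protocol". The split is fixed per cohort: "Within each block size of 15, 10 patients will be randomized to receive the MBI and 5 will be randomly assigned". No stratification, matching or minimization on a baseline variable is described.
- **Primary outcome and its baseline.** The Pain Catastrophizing Scale section states: "The PCS total score was the primary outcome". The Efficacy section under Assessments schedules each questionnaire at "week 0 (baseline, prior to initiation of treatment) and weeks 1, 3, and 6". This places baseline before treatment, not expressly before randomization.
- **Analysis.** The Efficacy section under Analytic approaches takes effect sizes from random coefficients regression models. It adds: "Tables for unadjusted mean scores for each condition by time will be presented". It states neither an adjustment for baseline nor an equal-baseline constraint.
- **Purpose.** Setting and sample says that "the focus of this pilot study is to estimate treatment effect sizes rather than to conduct statistical significance testing".

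**The concern.** Most small trials allocate patients on arrival, so future patients are unknown and strata stay part-filled. Here all 15 members of a cohort are known before anyone is allocated, so close balance on a baseline score could be had without changing the 10:5 split. The plan accepts the wait that batch randomization brings but uses the block to control arm size only.

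With 40 against 20 patients, a chance gap on the baseline of the primary outcome can be appreciable. It carries into the follow-up means in proportion to the correlation between visits, and through regression to the mean it also shifts a change or slope contrast in the opposite direction. Since the efficacy aim is to estimate the direction and size of an effect, what is at stake is the precision of that estimate and how readable the reported means are.

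**Working it through.** **Plan's own figures.** 4 cohorts × (10 + 5) = 40 + 20 = 60, which is consistent. The statement that power is below 80% has no effect size or SD behind it and cannot be reproduced as a number.

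**Inputs.** From the article: 40:20 in four 10:5 blocks; assessments at weeks 0, 1, 3 and 6. Assumed: normal scores with SD 1, the same correlation r between any two visits (r = 0.5 to 0.7), linear time, complete follow-up, no treatment effect.

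**1. Chance imbalance under the current draw.** SD of the baseline difference = √(1/40 + 1/20) = 0.274 SD.
P(|difference| > 0.3) = 2 × [1 − Φ(0.3/0.274)] = 27%.

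| Threshold (SD) | 0.2 | 0.25 | 0.3 | 0.4 | 0.5 |
|---|---|---|---|---|---|
| Probability | 47% | 36% | 27% | 14% | 7% |

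Simulating the actual 10:5 blocks gives SD 0.27 and 27% at 0.3 SD.

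**2. Balanced draw.** Each cohort is ranked by baseline PCS, five consecutive triplets are formed, and one control and two MBI patients are drawn in each. This gives 5 × (2:1) = 10:5 per cohort and 40:20 overall. Simulated SD of the baseline difference is 0.098 and P(> 0.3 SD) is 0.2–0.3%. The share of baseline-difference variance removed is k = 1 − (0.098/0.274)² = 0.87.

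**3. What that does to each estimate.** The variance reduction is k times the share of the estimate's variance explained by baseline.

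- *Unadjusted week-6 difference:* k × r² = 0.87 × 0.25 to 0.87 × 0.49, about 22% to 43%.
- *Change from baseline:* k × (1 − r)/2 = 0.87 × 0.25 to 0.87 × 0.15, about 22% down to 13%.
- *Linear slope:* mean time is 2.5, the sum of squares about it is 21, and the weight on week 0 is −2.5/21 = −0.119. The share is (1 − r) × 0.119² × 21 = 0.298 × (1 − r). Times k, this is about 13% at r = 0.5 and 8% at r = 0.7. The standard error falls by about 7% to 4% (√0.87 = 0.93; √0.92 = 0.96).
- *Week-6 difference adjusted for baseline:* about 0–1% by simulation. Chance imbalance inflates this variance by only about 1 + 1/57 = 1.02.

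**4. Size of the shift when the baseline gap is 0.3 SD.**

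- Raw follow-up difference: 0.3 × r = 0.15 to 0.21 SD.
- Change from baseline: 0.3 × (1 − r) = 0.15 down to 0.09 SD, in the opposite direction.
- Slope effect over 6 weeks: 6 × 0.119 × (1 − r) × 0.3 = 0.11 down to 0.06 SD, also opposite.
- Baseline-adjusted estimate: no expected shift.

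**5. Missing baseline forms.** If 25% of forms are not in at the draw and those patients are ranked at the cohort median, the SD of the baseline difference is about 0.17, P(> 0.3 SD) is about 8%, and the slope-variance gain falls to about 5–9%.

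**The case against.** The strongest reply is that nothing here is an error. Permuted blocks without stratification are valid, and the 27% is a property of any simply randomized 40:20 trial. That stands.

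Three further objections stand in part.

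- *The planned estimate is less exposed than the raw means.* Effect sizes come from the random coefficients model, and the table of means is descriptive and shows any baseline gap. So the 22–43% gain for the raw week-6 difference is not the gain for the plan's effect estimate; the slope figure of 8–13% is the closer guide.
- *Baseline PCS need not be in hand at the draw.* Only consent must precede it. Forms may come back by post or online, the Feasibility section under Assessments allows 2 weeks from recruitment, and the first payment can follow session 1 instead of receipt of baseline. The 15 patients are known at the draw; their scores may not be. Yet forms can come back while the cohort fills, and ranking late ones at the median avoids holding the draw, which answers the worry about idle time and early dropout.
- *Baseline handling may be settled in an analysis plan not shown.* It may, and its absence from the article is not a fault in itself. If the model does adjust, almost nothing is left to gain in precision.

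Two stronger readings are tempting. A reader might infer that the draw biases the result; it does not, since the imbalance averages zero over repeated draws. A reader might also infer that a chance gap could match the effect being sought; the article gives neither a target effect nor an SD for PCS, so this cannot be said.

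**Conclusion.** The point holds as an avoidable loss of precision, not as a flaw in validity. As written, the design leaves about a 27% chance of a baseline PCS gap above 0.3 SD, and the stated analysis does not say that the gap will be adjusted for. The cost to a linear slope contrast is modest: about 8–13% of its variance could have been removed by balancing, or 13–22% for change from baseline. It is about zero under full baseline adjustment. These percentages rest on equal visit correlations of 0.5 to 0.7, linear time and complete data, and the 0.3 SD threshold is a judgement. Because feasibility and acceptability form the first aim and efficacy is preliminary, the analysis change is worth making, and the change to the draw is an optional refinement.

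**What to change.** 1. **Analysis (Efficacy, under Analytic approaches).** State that the arm effect on PCS total will be estimated either with baseline PCS as a covariate and weeks 1, 3 and 6 as outcomes, or with all four visits as outcomes and the arm means constrained equal at baseline. The second form keeps patients who lack a baseline form. Keep the unadjusted table as description. This costs a sentence and gives nearly all the precision gain. Trial status says recruitment has ended, so it is the only part that can still be applied in this trial.

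2. **Draw (Randomization procedures), for a later trial with the same cohort design.** Ask for baseline PCS before the draw. Rank the 15 members by it, form five consecutive triplets, and randomly draw one control and two MBI patients in each. Place any patient whose form is not yet in at the cohort median, so that the draw is not held up. Keep baseline PCS in the model so that the standard error reflects the balance. This needs no extra patients or visits. The cost is some chasing of baseline forms before the draw, and balance weakens when forms are missing.

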### Retention strategies and compensation

In an attempt to prevent participants from dropping out before the MBI starts, a proactive retention strategy will be used to retain participants who have been randomized but have not yet participated in the MBI. Participants will receive weekly contact via telephone and email and will be provided with information regarding how many more participants are needed before the intervention will begin. After beginning the MBI program, participants randomized to the MBI will receive either a telephone call, a text message, or an email (their choice) on the morning of each mindfulness session and again 1 h before each session. In addition, all participants will receive weekly and biweekly contact from study personnel to remind them of their study participation, upcoming due dates for assessments, and when compensation checks have been mailed to their home address.

Three monetary payments will be provided to help increase retention and compensate participants for their time: (1) $10.00 after baseline assessments are received and/or participation in MBI session 1 has occurred, (2) $20.00 after receiving measurements at the end of week 3 and/or participation in MBI session 3, and (3) $30.00 at the conclusion of the study upon receiving the final measurements and/or participation in MBI session 6. All subjects in the in MBI and control groups will receive payments upon return of each assessment according to this schedule. In addition to providing monetary compensation, the MBI program will be provided at no cost to subjects, a value of over $400.00.

### Description of intervention arms

#### Mindfulness-based intervention condition

Participants randomized to the MBI condition will receive a telephonically delivered MBI program. The MBI adapts all core elements from John Kabat-Zinn’s original MBSR program [23] and targets common symptoms, emotions, and stressors related to chronic pain experienced by persons with SCD. We developed the telephonic MBI through an informal process that involved iterative feedback from patients, clinical experts in SCD and pain management, social workers, psychologists, and mindfulness clinicians. Through this process, relevant topics and skills were selected from the original MBSR program to adapt for each MBI session.

On the basis of needs described, and in line with adapting specific elements of MBSR, the original MBSR content was simplified and compressed into six 60-minute telephonic group sessions that teach (1) breath awareness (focus on breathing and observing thoughts without fighting or following them, weeks 1–6), (2) body scan (promoting mindfulness of sensations in different parts of the body, weeks 2–6), (3) walking meditation (walking as form of meditation, weeks 3–6), (4) loving-kindness (projection of friendliness and kindness toward oneself and others, weeks 4–6), and (5) choiceless awareness (awareness of all sensations with equal interest, weeks 5–6). Each of these practices, all of which are part of the original MBSR program, is focused on cultivation and practice of mindfulness techniques. Breath awareness, body scan, loving-kindness, walking meditation, and choiceless awareness promote and foster “open monitoring” and intentional observation of thoughts, feelings, and bodily sensations [13]. With guidance from the mindfulness instructor, participants will be presented with various examples of how each exercise can be infused with everyday tasks (e.g., doing the dishes, brushing teeth).

Currently, there is much debate on the mechanisms of how each of these practices may elicit changes for pain-related outcomes [15], but because the MBI contains components of exposure therapy, the walking meditation and body scan exercises may contribute to decreased pain-related disability by reducing fear of movement and fear of pain [24]. Researchers are actively engaged in trying to better understand the mechanisms of mindfulness and how mindfulness practices may specifically help those with pain [25–28].

Table 1 summarizes the intervention that will be used in this study and compares it with typical MBSR programs. The first 10 minutes of each session will be used to review previous material, followed by approximately 20 minutes of instruction and overview of a new mindfulness exercise and 15 minutes of mindfulness practice, with the remaining time used for questions. Because each session will be conducted as a group teleconference call, the size of each MBI session is limited to a maximum of ten patients (plus the mindfulness instructor) to minimize caller interruptions and disruptions.

**Table 1 Tab1:** Comparison between typical mindfulness-based stress reduction program and telephonic mindfulness-based intervention for persons with sickle cell disease

Week	MBSR	Telephonic MBI
1	Body scan	Mindful breathing
2	Breath awareness	Body scan
3	Sitting meditation, individual yoga	Loving-kindness
4	Stress coping	Mindful eating
5	Communication styles	Sensory awareness
6	Yoga, sitting meditation	Overview, conclusion
7	Loving-kindness	N/A
Weekend Retreat	Silent retreat	N/A
8	Wrap-up	N/A

*MBSR* Mindfulness-based stress reduction, *MBI* Mindfulness-based intervention, *N/A* Not applicable

This table provides a comparison of the standard 8-week MBSR program and the telephonic MBI that will be tested

Our decisions to reduce the number of minutes per session and remotely deliver the MBI are supported by the MBI literature. Prior studies have found time commitment to be a common barrier to recruitment and MBI completion [29, 30], as well as a nonsignificant correlation between the number of in-class hours and effect size of an MBI [31]. Therefore, first, the number of minutes per session has been reduced to 60, a length we believe is more amenable to the subject’s other obligations (e.g., work and family activities), and the number of weekly sessions has been reduced from eight to six. Second, it is difficult for some persons with SCD to find transportation to and from the clinic; therefore, an intervention that is easily accessible by telephone may increase the likelihood of recruitment, retention, and program completion. The literature supports the delivery of MBIs by telephone, with telephone vs. in-person interventions producing comparable outcomes [32–34]. Therefore, the six MBI sessions will be delivered telephonically instead of in person. In addition, the 2011 Pew Internet and American Life Project reported that approximately 87% of African Americans have cell phones and that 73% of individuals who make less than $10,000 per year have phones [35], providing support for the majority of persons with SCD being likely to have a phone.

The same MBI instructor will deliver all MBI sessions. The instructor is a healthcare professional and graduate of the University of Massachusetts Center for Mindfulness professional training program. In total, the instructor has more than 10 years of instructional experience in mindfulness, 2 years of experience in teaching telephone-based MBSR, and experience in leading groups for research studies.

Last, each 60-minute MBI session will require patients to call a toll-free 1-800 telephone number. The toll-free number does not require an access or login code; can accommodate up to 100 callers simultaneously; and can be accessed by telephone, Internet, and mobile app (iOS and Android only). The conference service used will be UberConference (Dialpad, San Francisco, CA, USA).

#### Wait-listed control condition

Patients randomized to the control condition will not receive the MBI but will receive treatment as usual. Treatment as usual consists of standard medication management as prescribed by the subject’s hematologist, primary care physician, psychologist, and/or any other medical professionals overseeing treatment.

Wait-listed patients will be offered the opportunity to cross over to the MBI condition once patients in the intervention arm complete six sessions. Patients who cross over from the wait-list to the MBI will participate in the same protocol as patients originally randomized to the MBI condition. The schedule of enrollment, interventions, and assessments of this study is shown in Fig. 1 and the Standard Protocol Items: Recommendations for Interventional Trials (SPIRIT) checklist (*see* Additional file 1).

**Fig. 1 Fig1:**
[figure not shown]
Schedule of enrollment, interventions, and assessments (formatted on the basis of the Standard Protocol Items: Recommendations for Interventional Trials [SPIRIT] 2013 template)

### Assessments

#### Demographic assessment

Sociodemographic data and clinical characteristics will be self-reported by participants and collected only at study enrollment (baseline). Participants will be asked to report their sex, age, race, genotype, socioeconomic status, educational history, hospital use (e.g., self-reported number of emergency department visits and hospital admissions over the last 2 years), and disease-related complications (e.g., stroke, acute chest syndrome, VOCs). These items have been used to assess sociodemographic and clinical characteristics of persons with SCD in prior studies [36, 37].

